### Hypothesis

Automated calculation and reporting of APRI and FIB-4 on routinely ordered blood tests and provision of information about liver cirrhosis, including a link for transient elastography referral, will increase the diagnosis of liver cirrhosis and linkage to specialist care.

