### Objectives

The primary objectives of this study are given below.

First, this study aims to measure the monthly rate and the number (proportion) of individuals with APRI greater than 1.0 and FIB-4 greater than 2.67 among people who undergo automated APRI and FIB-4 calculation on blood test events performed through a single Australian pathology service.

Second, this study aims to measure the monthly rate of transient elastography referrals received after the introduction of automated APRI and FIB-4 reporting, compared with the preintervention period.

Third, this study aims to measure the monthly rate and the number (proportion) of transient elastography tests performed in those with an elevated APRI and or FIB-4 score during the intervention period, compared with the preintervention period.

Fourth, this study aims to measure the monthly rate and the number (proportion) of individuals with APRI greater than 1.0 or FIB-4 greater than 2.67 that have cirrhosis range median stiffness (kPa) confirmed on FibroScan.

Finally, this study aims to measure the number (proportion) of individuals with cirrhosis range FibroScan during the intervention period that is linked to specialist care, compared with the preintervention period.

The secondary objective of this study is to describe the sociodemographic factors associated with (1) APRI greater than 1.0 and FIB-4 greater than 2.67, (2) attendance at FibroScan appointment, (3) cirrhosis diagnosed on FibroScan, and (4) linkage to specialist care.

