#### Study Setting

This study was conducted at the FibroScan clinic of a single tertiary center linked to a large pathology service, which provides both public and privately funded pathology services for the general population in regional and urban areas of Victoria, Australia.

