#### Intervention (In Addition to Standard of Care)

St Vincent’s Pathology automatically calculates and reports APRI and FIB-4 scores if platelet count, alanine transferase (ALT) level, and AST level are requested together in a single blood test by primary care physicians. This is provided free of charge. The result will be reported to the requesting primary care physician (both in paper format and online), along with a brief interpretation of the APRI and FIB-4 results, their relevance to liver cirrhosis screening, and a web link for further web-based information. No additional testing or appointments are scheduled as part of this study in addition to the standard of care.

Two separate pathways will be used by St Vincent’s Pathology to notify clinicians of our new APRI and FIB-4 reporting format approximately 1 month prior to the commencement of the intervention period. (1) The St Vincent’s Pathology standard liver function test result report will include a comment stating that APRI and FIB-4 scores will be reported as of the date of project commencement. (2) There will be a new banner included on the St Vincent’s Pathology website notifying clinicians of the availability of automatic reporting of APRI and FIB-4 scores on blood test events and the date that this reporting will commence. This will have a web link to further information on the APRI and FIB-4 score, as well as information about chronic liver disease.

The additional information on the website includes (1) how APRI and FIB-4 are calculated and how it is used, (2) how to interpret the APRI and FIB-4 result, (3) what further tests would be recommended if someone has an abnormal APRI result, (4) further general information about chronic liver disease and liver cirrhosis, and (5) a link to a web-based referral form for the St Vincent’s Hospital FibroScan service to book a confirmatory FibroScan to determine whether the patient has liver cirrhosis.

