### Study Timeline

#### Preintervention Period

Between August 1, 2023, and January 31, 2024, St Vincent’s Pathology will prospectively collect data on all ALT, AST, and platelet count test results conducted, and APRI and FIB-4 scores will be automatically calculated by the St Vincent’s Pathology data management system, but not reported to the ordering clinician. These data will be prospectively collected from St Vincent’s Pathology by a member of the study team, along with exposure variables outlined above. During the same time period, outcome measures per month will be prospectively collected from the St Vincent’s hospital electronic medical records by a member of the research team (number of FibroScan referrals, number [proportion] of scheduled FibroScan appointments attended, number [proportion] diagnosed with cirrhosis, and number [proportion] linked to specialist care).

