### Statistical Analysis Plan

#### Outcome Measures

Data will be analyzed per test event and per individual tested.

Primary outcomes of this study include the number of APRI and FIB-4 scores calculated on blood test events conducted during the study period, overall and per month; the number (proportion) of APRI scores that are greater than 1.0 and FIB-4 scores that are greater than 2.67; number of FibroScan referrals overall and per month, operationalized as number of completed FibroScan referrals generated online using the recommended St Vincent’s Pathology FibroScan referral link on the request slip, or St Vincent’s Pathology APRI or FIB-4 calculation web page referral form link; number of individuals with an APRI greater than 1.0 or FIB-4 score greater than 2.67 who undergo a FibroScan test at St Vincent’s Hospital Melbourne overall and per month; proportion of individuals with an APRI greater than 1.0 or FIB-4 score greater than 2.67 who undergo a FibroScan test at St Vincent’s Hospital Melbourne; the number of individuals per month who undergo FibroScan at St Vincent’s Hospital Melbourne who have cirrhosis diagnosed (liver stiffness measurement >12.5kPa); the number (proportion) of individuals with an APRI greater than 1.0 or FIB-4 score greater than 2.67 who have cirrhosis confirmed by FibroScan; the number (proportion) of individuals with etiology-specific cirrhosis range FibroScan results that are referred to the specialist liver clinic; and the number (proportion) of individuals with etiology-specific cirrhosis range FibroScan results that attend to the specialist liver clinic appointment.

The secondary outcomes of this study include the number (proportion) of individuals, stratified by age category, sex, and postcode who have elevated APRI greater than 1.0 and FIB-4 score greater than 2.67, attend the FibroScan clinic for further testing, have etiology-specific cirrhosis range FibroScan scores (kPa), and attend a liver specialist clinic appointment.

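### Scans and cirrhosis diagnoses are counted at one hospital only, and the intervention steers referrals to that hospital, so a rise cannot be separated from redirection between providers

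*Protocol article*

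**What the plan says.** **Where events are counted.** In the protocol article, Outcome Measures counts people with an elevated APRI or FIB-4 "who undergo a FibroScan test at St Vincent’s Hospital Melbourne overall and per month". The monthly cirrhosis outcome is the number "who undergo FibroScan at St Vincent’s Hospital Melbourne who have cirrhosis diagnosed". The clinic outcome names no hospital; it counts those with a cirrhosis-range result "that attend to the specialist liver clinic appointment".

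**Data source.** Under Preintervention Period, "outcome measures per month will be prospectively collected from the St Vincent’s hospital electronic medical records"; the list covers referrals, attendance, diagnosis and linkage. No other source is named anywhere.

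**Who is tested.** Study Setting says that the pathology service "provides both public and privately funded pathology services for the general population in regional and urban areas of Victoria, Australia".

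**What the intervention adds.** The web information includes "a link to a web-based referral form for the St Vincent’s Hospital FibroScan service to book a confirmatory FibroScan". Intervention Period puts a link to such a form on the reports as well. Before February 1, 2024, referral was by paper and fax (Comparator Group).

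**What is to be concluded.** The Hypothesis is that the package "will increase the diagnosis of liver cirrhosis and linkage to specialist care", with no site limit. The third and fourth primary objectives, on scans performed and on confirmed cirrhosis, also name no hospital. The secondary objective is to "describe the sociodemographic factors associated with" elevated scores, attendance, cirrhosis and linkage. Analysis Methods tests urban or regional residence against each of these.

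**The concern.** The intervention may change two things at the same date: whether a person is scanned, and whether a scan is visible to the study. A person who would have been scanned elsewhere before February 2024 counts as unscanned. The same person sent through the link counts as scanned and, where the stiffness is high enough, as diagnosed. Conversely, the new report recommends elastography in general terms, so it may prompt scans at other sites that are never counted.

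The comparison is pre-post with no concurrent control, and the link starts on the date that divides the periods. A model with a break at that date therefore cannot tell the two mechanisms apart. The Strengths and Limitations section does not raise the matter.

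At stake is what a positive result may be said to show: more cirrhosis found among the people tested, or more use of one hospital's service. Capture may also differ by residence, which affects the urban-versus-regional comparison.

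**Working it through.** The plan gives no figure for the share of this population's scans done at St Vincent's, so there is nothing to reproduce on this point. The sample size of 1,100 per subgroup does not enter.

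**Inputs**
- From Results and Table 1: 816 individuals with elevated FIB-4 and 446 with elevated APRI in the preintervention data. The group with either score elevated therefore lies between 816 (full overlap) and 446 + 816 = 1,262 (no overlap). I use n = 816 in each period.
- Assumed, not in the documents: the true scan rate at any site, t, and St Vincent's share of scans before and after, s and s′.

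**Step 1. Redirection with no true change.** Recorded rate = t × share, so the recorded ratio is s′/s. With t = 10%, s = 50% and s′ = 80%, the recorded rates are 5.0% and 8.0%, or 816 × 0.05 = 41 and 816 × 0.08 = 65 scans. The ratio is 1.6 where the true ratio is 1.0.

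The chance of a significant increase in a simple two-sided 5% comparison of two proportions is Φ(z), with z = [d − 1.96·√(2p̄(1−p̄)/n)] / √([p₁(1−p₁)+p₂(1−p₂)]/n). Here d = 0.03 and p̄ = 0.065, so z = (0.03 − 1.96 × 0.01220)/0.01218 = 0.50 and Φ(z) = 69%. This test stands in for the planned regression models.

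| Assumed share, before to after | Recorded scans at t = 10% | Ratio | Chance of significance at t = 5% / 10% / 20% |
|---|---|---|---|
| 30% to 60% | 24 to 49 | 2.0 | 53% / 83% / 99% |
| 50% to 80% | 41 to 65 | 1.6 | 40% / 69% / 95% |
| 70% to 90% | 57 to 73 | 1.29 | 18% / 32% / 60% |

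Smaller shifts matter less: 50% to 60% gives 0.60/0.50 = 1.20, and 70% to 80% gives 0.80/0.70 = 1.14. With n = 1,262, the 50% to 80% case at t = 10% has an 86% chance of significance. If the yield per scan is constant, diagnoses rise by the same ratios. At an assumed yield of 20%, 41 and 65 scans give about 8 and 13 diagnoses.

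**Step 2. The opposite direction.** In general the recorded ratio is (t′s′)/(ts). Suppose that the report doubles true scanning from 10% to 20%, but many of the extra scans are done elsewhere and the share falls from 70% to 50%. The recorded rates are then 7% and 10%, a ratio of 1.43 against a true 2.0. The net direction is not fixed by the design.

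**Step 3. Which outcomes are exposed.** Let c be the proportion of scans in the cirrhosis range and l the proportion of those who are linked.
- Number scanned = n·t·s; number diagnosed = n·t·s·c; number linked = n·t·s·c·l. All contain s.
- Proportion of people with elevated scores who are scanned = t·s; proportion confirmed = t·s·c. Both contain s.
- Proportion linked among cirrhosis-range scans = (n·t·s·c·l)/(n·t·s·c) = l. Here s cancels, and redirection can act only through a change in case mix.

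**Step 4. Residence.** If true scanning is equal but St Vincent's does an assumed 80% of urban and 40% of regional scans, the recorded regional-to-urban ratio among people with elevated scores is 0.40/0.80 = 0.5 instead of 1.0. The same holds for confirmed cirrhosis if the yield is equal.

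**The case against.** The strongest reply is that little of this is hidden. The abstract calls the study single-center, the setting is one FibroScan clinic, it is a pilot, and the link is a declared part of the package. The scan and monthly diagnosis outcomes already name the hospital. The Background also describes access to elastography as limited, so few scans may occur elsewhere, and no passage shows that any do. This stands as far as size is concerned. It does not settle the claim, because the hypothesis and the third and fourth primary objectives drop the site limit that the outcomes carry.

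Four stronger readings are tempting, and the documents do not support them.
- A reader might infer that redirection inflates the linkage proportion. Step 3 shows that it does not do so mechanically. That clinic visits count only at St Vincent's is itself an inference from the single named data source.
- A reader might infer that regional people will necessarily show lower attendance and linkage. Preintervention Period and Analysis Methods also describe attendance among scheduled or referred appointments. On that basis, someone scanned locally without a St Vincent's booking is not a non-attender. The exposure is in scanning and confirmed cirrhosis among all people with elevated scores, where a difference can arise from ascertainment alone.
- A reader might infer that any rise would be spurious. Some referrals through the link will probably be new scans, and Step 2 shows that bias towards no effect is also possible.
- A reader might set the ratios above against the 10% difference in Sample Size Justification. That figure concerns referrals and is not said to be relative or absolute, so the two are not comparable.

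**Conclusion.** The concern holds in a limited form. Scans and monthly cirrhosis diagnoses are counted at one hospital, the only named data source is that hospital's records, and the intervention directs referrals there from the date that divides the two periods. The counts of scans, diagnoses and linked people, and the proportion of people with elevated scores who are scanned or confirmed, can therefore change without any change in true scanning. The urban-versus-regional comparison of scanning and confirmed cirrhosis has the same weakness.

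Size and net direction are unknown. The illustrated ratios of 1.14 to 2.0 rest entirely on assumed shares and on an unchanged true scan rate; they show what could happen, not what is likely. The plan describes no means of separating redirection from added diagnosis, so a rise would support a statement about use of St Vincent's services and not, by itself, one about diagnosis in the tested population.

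**What to change.** 1. Restate the hypothesis, the third and fourth primary objectives and the planned conclusion as scans, cirrhosis-range results and clinic linkage at St Vincent's Hospital, not as diagnosis and linkage in the tested population. Say in the limitations that a rise cannot be separated from redirection between providers, and that scans prompted at other sites are not seen.
2. Limit the urban-versus-regional inference to the prevalence of elevated APRI and FIB-4, which does not depend on where a scan is done. Otherwise report the scanning, diagnosis and clinic comparisons by residence only as use of one site's service.

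Both are changes of wording and reporting and need no new data. The cost is a narrower claim. Restricting the primary comparison to the hospital's catchment would not be a substitute: people living near the hospital can be redirected too, and choosing areas by their preintervention referrals selects on the baseline outcome. Restricting it to practices that already referred would need a practice identifier, which is not among the listed variables.

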#### Exposure Variables Collected

Sex, age category (deciles), socioeconomic status of residence (defined by Australian Bureau of Statistics Socio-Economic Index Areas [SEIS] data matched to postcode), urban versus regional place of residence (defined by SEIS data matched to postcode), and liver disease indication recorded on FibroScan requests will be collected.

### Analysis Methods

The number of APRI and FIB-4 scores generated and the proportion of APRI and FIB-4 scores in the cirrhosis range will be described overall and rates per month will be calculated.

The number (proportion) of individuals with an elevated APRI or FIB-4 who are referred for a FibroScan will be described overall and per month; and the number of FibroScan referrals after the intervention will be compared with the number of FibroScan referrals prior to the intervention by logistic regression modeling (time series analysis with the timepoint of interruption defined as February 1, 2024, when the reported APRI score intervention was introduced).

Similarly, the number (proportion) of individuals with an elevated APRI or FIB-4 who are referred for a FibroScan and who attend their FibroScan appointment, overall and per month, will be described and compared with the number (proportion) of FibroScan appointments attended prior to intervention using linear regression modeling, as well as the number (proportion) of individuals with FibroScan results in cirrhosis range that are referred and attend specialist liver clinic appointments.

The number and proportion of individuals with an elevated APRI or FIB-4 who had cirrhosis confirmed by FibroScan will be described, and sensitivity, specificity, and positive and negative predictive values of APRI for cirrhosis determined by confusion matrix. The area under the receiver operating characteristic curve of APRI and FIB-4 for cirrhosis diagnosis will also be calculated by receiver operating characteristic analysis.

The bivariate distribution of sociodemographic (sex, age category, and urban or regional place of residence [defined by postcode using SEIS data]) and clinical variables (liver disease indication) within the proportion of people with elevated APRI and FIB-4 score, who attend FibroScan testing, have elevated FibroScan results, and attend the liver specialist clinic will be determined and compared with their counterparts using chi-square test for categorical data, 2-tailed Student *t* test for parametric continuous data, and Wilcoxon rank-sum test for nonparametric continuous data as appropriate.

A 2-tailed *P* value of .05 will be used as the significance threshold for all analyses. All analyses will be performed using STATA (version 17; Stata Corporation).

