**Methods:**

We have partnered with a large pathology service in Victoria, Australia, to pilot a population-level liver cirrhosis screening package, which comprises (1) automated calculation and reporting of APRI and FIB-4 on routinely ordered blood tests; (2) provision of brief information about liver cirrhosis; and (3) a web link for transient elastography referral. APRI and FIB-4 will be prospectively calculated on all community-ordered pathology results in adults attending a single pathology service. This single-center, prospective, single-arm, pre-post study will compare the monthly rates of transient elastography (FibroScan) referral, liver cirrhosis diagnosis, and the proportion linked to specialist care in the 6 months after intervention to the 6 months prior to the intervention.

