### Recruitment

All individuals aged 18 years and older who have liver function tests and full blood count requested by a community-based health worker and performed at St Vincent’s Pathology between August 1, 2023, and July 31, 2024, will be recruited. There will be no active recruitment of participants for this study.

This study is an evaluation of a health system–wide introduction of routine reporting of APRI calculation, information on liver cirrhosis, and a web link through St Vincent’s Pathology to improve the quality of care for people with liver disease; therefore, no individuals will individually consent to participate. No personally identifying information will be collected and all data supplied to the research team will be deidentified by St Vincent’s Pathology and transient elastography booking and reporting teams, respectively. Variables including 10-year age category, sex, and postcode will be collected as part of the study but will not allow identification of individuals, as they are broad categories expected to contain more than 1000 persons per strata per month during the study period.

The exclusion criteria of this study include children aged 18 years or younger and blood tests performed during a hospital inpatient stay, or requested by hospital outpatient service, defined by St Vincent’s Pathology records (blood collection site).

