### Sample Size Justification

We have conducted a preliminary analysis of the number of AST and platelet count testing events that were performed at St Vincent’s Pathology over a 12-month period (2019). These data showed approximately 11,000 people known to St Vincent’s hospital clinics, and a further 4400 people in the community that had AST and platelet count testing events, that would have allowed APRI calculation to be performed, proving the feasibility of reaching large numbers within the community for cirrhosis screening.

For the comparison of rate of referral for FibroScan before and after the intervention, we estimate that we will be powered to detect a 10% difference in rates of FibroScan referral before and after the intervention. For the logistic regression analyses to determine the difference in proportion of APRI scores leading to referral before and after providing cirrhosis information and FibroScan referral link information (overall and by subgroup), and for determining the proportion of FibroScan referrals that are attended (overall and by subgroup), we are powered to detect a 5% or greater difference between the intervention and historical control groups with power 90% and a sample size of 1100 per subgroup. The above numbers of more than 15,400 individuals having APRI calculations within 12 months suggest that we will be adequately powered to explore our end points including stratified by sex, urban versus rural place of residence, age category, socioeconomic quartile of place of residence, and indication for FibroScan (all of which are expected to have >1000 individuals in each subgroup).

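### The person-level before-after comparisons name no adjustment for patient characteristics collected in both phases, so a case-mix change could be read as an intervention effect

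*Protocol article*

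**What the plan says.** **Design.** The abstract's Methods state: "This single-center, prospective, single-arm, pre-post study will compare the monthly rates". The pre-phase runs from August 1, 2023 to January 31, 2024, and the intervention phase from February 1 to July 31, 2024.

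**Comparative models (Analysis Methods).**
- For referrals, "the number of FibroScan referrals after the intervention will be compared with the number of FibroScan referrals prior to the intervention by logistic regression modeling", described as a "time series analysis with the timepoint of interruption defined as February 1, 2024".
- Attendance is "compared with the number (proportion) of FibroScan appointments attended prior to intervention using linear regression modeling", and the same sentence covers specialist linkage.
- No patient covariate is named for either model.

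**Sample Size Justification.** This section describes logistic regression for the "difference in proportion of APRI scores leading to referral before and after providing cirrhosis information and FibroScan referral link information". The comparison is to be made for the whole group as well as within strata, and attended referrals are treated in the same way. The strata listed are sex, urban or rural residence, age category, socioeconomic quartile and indication for FibroScan.

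**Variables held.**
- Exposure Variables Collected begins "Sex, age category (deciles), socioeconomic status of residence" and adds urban or regional residence.
- Recruitment, which spans both phases, says: "Variables including 10-year age category, sex, and postcode will be collected as part of the study".
- The Preintervention Period section has the laboratory results collected "along with exposure variables outlined above".
- The Comparator Group section has both scores calculated from the start of the study.

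**Stated uses of these variables.** Analysis Methods gives bivariate chi-square, t or rank-sum tests. Outcome Measures and Sample Size Justification give stratified results. Strengths and Limitations does not mention confounding of the before-after contrast.

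**The concern.** Nothing balances the two phases. The people analysed in each are those who happened to have the three blood tests ordered together in that half-year. If the intervention-phase screen-positives differ from the earlier ones in score level, age or place of residence, the proportions referred, scanned or attending can change with no effect of reporting. A change in the other direction could hide a real effect.

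The document gives two reasons to take this seriously, though neither shows that a shift occurred:
- August to January is set against February to July, so season and phase are fully confounded.
- Clinicians are told about a month beforehand that scores are coming, and scores exist only when platelets, ALT and AST are requested together. The announcement could change who is tested.

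The measured part of such a change can be removed with data the study already plans to hold. No such use is stated for the overall estimate.

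**Working it through.** **1. The plan's own figure.** Sample Size Justification gives 1100 per subgroup for a 5% difference (read here as 5 percentage points) with 90% power. Analysis Methods gives two-sided 0.05. No baseline proportion is stated. The formula is

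n per group = [1.96·√(2p̄(1−p̄)) + 1.2816·√(p₁(1−p₁) + p₂(1−p₂))]² / (p₂−p₁)²

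- 5% vs 10%: 582
- 10% vs 15%: 918
- 12.5% vs 17.5%: 1070 (1110 with continuity correction)
- 13% vs 18%: 1099
- 20% vs 25%: 1464

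The figure of 1100 is recovered only near a baseline of 12% to 13%, so it can be neither confirmed nor refuted. The present point does not depend on it. The 5 points serve only as a yardstick below.

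**2. Which comparisons are affected.**

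| Comparison | Before-after model stated | Can person-level covariates enter? |
|---|---|---|
| Monthly number of referrals | Logistic regression, interrupted time series | No, only monthly composition |
| Proportion of scores leading to referral | Logistic regression | Yes |
| Attendance at FibroScan (number and proportion) | Linear regression | Yes, for the proportion |
| Proportion of elevated-score individuals scanned | Comparison in Objectives, no separate model | Yes |
| Specialist linkage | In the linear-regression sentence | Yes, but few events are likely |
| Cirrhosis confirmed in elevated-score individuals | None, described only | Not applicable |

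**3. Size of the screen-positive group.** The Results report 446 individuals with elevated APRI and 816 with elevated FIB-4. Either score elevated is therefore at least 816 and at most 446 + 816 = 1262.

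**4. What a shift would do (illustration, all rates assumed).** Split screen-positives into low- and high-referral strata with rates p_L and p_H, identical in both phases, so there is no true effect. With high-stratum share s, the crude proportion is (1−s)·p_L + s·p_H. Example with p_L = 5% and p_H = 20%:
- s = 30%: 0.70×5% + 0.30×20% = 9.5%
- s = 40%: 0.60×5% + 0.40×20% = 11.0%
- Difference 1.5 points; odds ratio (0.110/0.890)/(0.095/0.905) = 1.18

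The last column of the table is the chance that a nominal 5% two-sample z test rejects, for 816 to 1262 per phase.

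| High-stratum share | p_L, p_H | Crude difference (points) | Crude odds ratio | Rejection |
|---|---|---|---|---|
| 30% → 35% | 5%, 10% | 0.25 | 1.04 | 5.5–5.7% |
| 30% → 35% | 10%, 40% | 1.5 | 1.10 | 12–16% |
| 30% → 40% | 5%, 10% | 0.5 | 1.08 | 7–8% |
| 30% → 40% | 5%, 20% | 1.5 | 1.18 | 17–24% |
| 30% → 40% | 10%, 40% | 3.0 | 1.20 | 32–46% |
| 30% → 50% | 5%, 10% | 1.0 | 1.17 | 12–17% |
| 30% → 50% | 10%, 40% | 6.0 | 1.42 | 83–95% |

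Against the 5-point yardstick, a 10-point shift in mix accounts for 0.5/5 = 10% to 3/5 = 60%. A 5-point shift does little.

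**5. What adjustment does here.** Within each stratum the phase difference is zero, so a difference standardised to any common mix is also zero, whatever the shift. This holds only for characteristics that are measured and modelled.

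**The case against.** **The article is silent rather than wrong.** A reader might infer that the regressions contain no patient covariates. The article does not say so. It lists no model terms beyond the interruption, and a fuller plan may list more. What stands is narrower: the article states what the collected variables are for, and adjusting the overall estimate is not among those uses.

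**The variables are used beyond bivariate tests.** This is correct. Subgroup analyses by sex, age, residence, socioeconomic quartile and indication are planned, and they could reveal a shift one variable at a time. They do not adjust the overall estimate, and score level is not among the strata.

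**Referral counts do not take person-level covariates.** This is also correct. In the interrupted series a pre-trend term could absorb gradual drift, though not an abrupt or seasonal change.

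**Adjustment cannot rescue the referral outcome as defined.** Outcome Measures counts referrals completed through the online link, while the Comparator Group section describes faxed paper referrals before the intervention. On that definition the pre-phase value would be close to zero by construction. The objection stands in full. It is a separate problem, which the fix here leaves untouched.

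**Nothing shows a shift.** Both phases use the same laboratory and the same eligibility rules, in adjacent windows. This stands too, and it limits the claim to what could happen.

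**Conclusion.** The point holds for the person-level comparisons: the proportion of elevated-score individuals referred or scanned, attendance, and linkage where numbers allow. As written, their overall before-after estimates are crude in a non-randomised design whose phases share no calendar month, although relevant variables are collected in both. The possible error cannot be quantified from the documents. Under the assumed rates it runs from negligible (5-point shift in mix, odds ratio 1.04 to 1.10) to material (20-point shift, 1.17 to 1.42).

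A reader might go further and conclude that the study's result will be biased, or that the confirmed-cirrhosis analysis is affected. The documents support neither. No shift is shown, and confirmed cirrhosis is only described, with no before-after model. That score level predicts referral strongly is an expectation, not a figure in the article. Adjustment would also leave unmeasured differences and seasonal changes in referral behaviour in place. This is a worthwhile improvement to make before analysis, not a fatal flaw.

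**What to change.** Add to Analysis Methods, for the person-level proportion models only:

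- A prespecified adjustment set: score level (one score term, or both if they are not collinear, since both come from the same blood tests), age category, sex, urban or regional residence, and socioeconomic quartile.
- The adjusted before-after difference, standardised to a common case mix, reported beside the crude one. If the announcement itself changes who is tested, the two answer different questions, so both are needed.
- Where events are few, as is likely for specialist linkage, score level, age and sex only, or the crude result alone.
- Liver disease indication left out of the set, because it is recorded only on FibroScan requests.
- A statement that the monthly referral-count series is outside this change, and a line in the limitations on residual confounding and season.

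The cost is slightly more analysis work and no new data collection. Residence and socioeconomic area must be matched from postcode, as already planned. The models also depend on linking pathology to hospital records, which the Results report as under way and which the scanning outcome needs in any case.
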